**10.5.2 Safety**

Safety variables will be analyzed separately for the safety population a) for the period between Week 7 (Baseline 2) and Month 6 (or date of premature discontinuation of the study), b) for the period between Baseline 1 and Baseline 2, and c) for the total treatment period (Baseline 1 (prior to Tx) to Month 6).

The safety variables will be as follows:

- Incidence and severity of Adverse Events (AEs) and Serious Adverse Events (SAEs)
- Incidence of infections
- Incidence of tumors
- Changes in cardiovascular risk (Framingham Score)
- Occurrence of proteinuria
- Incidence of new onset of diabetes mellitus (NODM)

## **AEs/Infections/Tumors**

Generally, infections and tumor data are analyzed together with AE data. In addition, infection and tumor data will be analyzed and presented separately.

Data collected by AE CRFs and by Infection CRFs are to be coded with the MedDRA dictionary that gives preferred term and body system information. The incidence of AE will be summarized by body system, preferred term, severity, and relationship to study drug. All information pertaining to AE noted during the study will be listed by treatment group and patient, detailing verbatim given by the investigator, the preferred term, the body system, start/end dates, severity, seriousness, relationship to study drug and action taken. The AE onset will also be shown relative (in number of days) to the day of initial dose per study period (within the first 6 weeks, after BL2).

In addition to being analyzed similarly as AE, as described above, the relative frequency of infections by type and micro-organism will be tabulated as well as the frequency of tumors by affected organ.

AE occurring 7 or more days after the discontinuation of study medication will not be considered as treatment-emergent and will not be included in AE/infection summary tables.

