clinical studies with favorable results (Fabrizii et al. 2005, Hong et al. 1999, Emparan et al. 2004). It has been shown that Basiliximab, a chimeric monoclonal antibody directed to the  $\alpha$ -chain of the interleukin-2 receptor, expressed on the surface of activated T lymphocytes, significantly reduced the incidence of acute rejection (Nashan et al., 1997; Kahan et al., 1999, Ponticelli et al., 2001). Therefore, patients received in addition to an immunosuppressive therapy of cyclosporine and corticosteroids with or without azathioprine a concomitant medication of 20mg basiliximab by i.v. infusion preoperatively and 20mg on day 4 after transplantation. With this application scheme of 40mg basiliximab an adequate receptor saturation defined as a serum concentration more than 0.2  $\mu$ g/ml was maintained for  $36 \pm 14$  days and a basiliximab clearance of  $36.7 \pm 15.2$  ml/hr was observed (Kovarik et al., 1999). Interestingly, Kovarik and co-workers revealed a significantly lower clearance of basiliximab in patients treated with triple immunosuppression consisting of cyclosporine, corticosteroids and mycophenolate mofetil resulting in a prolonged duration of CD25 saturation ( $59 \pm 17$  days) compared with a dual therapy (Kovarik et al., 2001). No data is available concerning the influence of mycophenolic acid on a single dose of 20mg basiliximab but it can be assumed that the period of IL-2 receptor blockade of  $20 \pm 7$  days in patients receiving only one injection of basiliximab is extended under concomitant administration of mycophenolic acid (Kovarik et al., 1999). Nevertheless, the induction therapy with IL-2R antibodies has become the standard of care in many centers because they allow for better rejection prophylaxis despite lower CNI levels, thereby substantially reducing the nephrotoxic potential of the immunosuppressive regimen (Ekberg et al. 2007). While the reduction of the potential nephrotoxic CNIs is performed in many centers under the umbrella of induction therapy e.g. with IL-2R antibodies, other centers prefer the complete avoidance of CNIs or the delayed administration of CNIs in order to prevent the development of DGF. As pointed out, the complete avoidance of CNIs was not successful in large prospective randomized trials (Ekberg et al. 2007). Similarly, the delayed administration of the potentially nephrotoxic CNIs provided no benefit on incidence of DGF in patients at risk of developing DGF (Kamar et al. 2006). Importantly, delayed administration of CsA was not associated with better graft function, but resulted (although not significantly) in a higher incidence of acute rejection (15,5% vs. 26,5%). The lack of benefit for a delayed introduction of CNIs was confirmed in two additional prospective randomized studies conducted on adult patients (Mourad G et al. 2001, Andres et al. ESOT 2007 Senior study). In summary, the delayed use of CNIs is not advantageous, and even may predispose to higher rejection rates, especially in the highly mismatched participants of the ESP Program (Fritsche et al. 2003). Because restoration of renal function in organs from older donors is important, and because these organs tend to be more fragile and more susceptible to the long-term consequences of the nephrotoxic effects of calcineurin inhibitors (Meier-Kriesche et al. 2000) an early conversion to a CNI-free regimen may be advisable, because all attempts to delay or avoid CNIs were not successful yet.

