**Group 2: Control maintain prior immunosuppressive regimen consisting of Myfortic® + Sandimmun® Optoral**

In group 1, step 1 of the therapy switch will be performed the day after randomization and will be continued on Day 2 with step 2. The therapy switch will be completed on Day 3 with step 3.

Patients randomized to Certican group will receive two additional doses of Simulect® (each 20 mg) as rejection prophylaxis on Week 7 and 12.

The established treatment will be continued until month 6 (final assessment of the core trial). Control assessments will be performed at Week 12, 18 and 24 (end of study and early discontinuation) post Tx. Renal function (creatinine, GFR) as well as safety and efficacy measures will be assessed at every study visit.

In the event of suspected acute rejections, renal biopsies will be performed.

Additionally, on day 7 ± 2 after randomization a blood level control will be performed.

Statistical analysis and report writing will be performed when all patients have completed Month 6 after Tx assessment (or discontinued the study prematurely).

An independent Safety-Monitoring-Board will review the safety data every 3 months during the recruitment phase and every 6 months thereafter, until all patients have completed the study treatment (Month 6).

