#### 6.5.5 Study drug discontinuation

In case of a platelet count  $<75,000/\text{mm}^3$ , a leukocyte count  $<2,500/\text{mm}^3$  or a neutrophil count  $<1,500/\text{mm}^3$ , at the discretion of the investigator, Myfortic® medication dose may be reduced by half, or eliminated completely until the event resolves. In case of dose reduction, Myfortic® should be reduced according to the guidelines given in [Appendix 4](#). In the CNI-free group, Certican® should be continued on a stable dose level and reduced only if the symptoms do not respond to the reduction of the Myfortic® dosage.

In case of elevated cholesterol and/or triglyceride levels, lipid lowering medications should be maximized. If the elevation persists, the dosing of Certican® should be adjusted following the recommendations given in [Appendix 4](#).

Dose reduction may be performed for those patients with other moderate/severe AEs according to the investigators' judgment. Also in these cases, the medication doses can be reduced by half or interrupted completely until event resolves.

If the Myfortic® or Certican® medication is interrupted for more than 2 consecutive weeks or more than 4 cumulative weeks within the 6 months study treatment, discontinuation of the respective medication should be considered and the patient withdrawn from the study.

Patients who discontinue study treatment before completing the 6-month period should be scheduled for a the end of study visit as soon as possible, at which time all of the assessments listed for the end of study visit (Visit 6, Month 6) will be performed.

All patients who discontinue study drug, including those who refuse to return for a final visit, will be contacted for safety evaluations during the 30 days following the last dose of study drug taken.

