### **Adverse events**

An adverse event is the appearance or worsening of any undesirable sign, symptom, or medical condition occurring after obtaining informed consent even if the event is not considered to be related to study drug. Study drug includes the investigational drug under evaluation and the comparator drug or placebo that is given during any phase of the trial. Medical conditions/diseases present before starting study drug are only considered adverse events if they worsen after starting study drug. Abnormal laboratory values or test results constitute adverse events only if they induce clinical signs or symptoms, are considered clinically significant, or require therapy.

The occurrence of adverse events should be sought by non-directive questioning of the patient at each visit during the study. Adverse events also may be detected when they are volunteered by the patient during or between visits or through physical examination, laboratory test, or other assessments. As far as possible, each adverse event should be evaluated to determine:

1. the severity grade (mild, moderate, severe)
2. its relationship to the study drug (Certican®, Simulect® dose 3 & 4)  
(suspected/not suspected)
3. its duration (start and end dates or if continuing at final exam)
4. action taken i.e:
  - (a) no action taken;
  - (b) study drug dosage adjusted/temporarily interrupted;
  - (c) study drug permanently discontinued due to this adverse event;
  - (d) concomitant medication taken;
  - (e) non-drug therapy given;
  - (f) hospitalization/prolonged hospitalization)
5. whether it is serious, where a serious adverse event (SAE) is defined as one which:
  - is fatal or life-threatening
  - results in persistent or significant disability/incapacity
  - constitutes a congenital anomaly/birth defect
  - requires inpatient hospitalization or prolongation of existing hospitalization, unless hospitalization is for:
    - routine treatment or monitoring of the studied indication, not associated with any deterioration in condition

- elective or pre-planned treatment for a pre-existing condition that is unrelated to the indication under study and has not worsened since the start of study drug
- treatment on an emergency outpatient basis for an event not fulfilling any of the definitions of a SAE given above and not resulting in hospital admission
- social reasons and respite care in the absence of any deterioration in the patient's general condition

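### AE relatedness is asked only for drugs of the Certican arm, and the AE and infection tables omit events from day 7 after stopping that the protocol still collects

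*Protocol*

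**What the plan says.** **Relatedness.** Section 7.6 (Adverse events), item 2, has the investigator judge "its relationship to the study drug" and names in brackets only Certican and Simulect doses 3 and 4. The paragraph that opens the same subsection is wider: "Study drug includes the investigational drug under evaluation and the comparator drug or placebo". The Glossary also counts control drugs as study drug. Section 10.5.2 plans a summary of AE incidence by relationship to study drug, and Section 10 has all summaries presented by treatment group.

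**Extra basiliximab.** Section 4: "Patients randomized to Certican group will receive two additional doses of Simulect", at Weeks 7 and 12. The control arm gets only the two induction doses.

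**Seven-day rule.** Section 10.5.2 (AEs/Infections/Tumors) says that "AE occurring 7 or more days after the discontinuation of study medication will not be considered as treatment-emergent" and that these events "will not be included in AE/infection summary tables".

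**What is collected after stopping.** Under Section 6.5.5, patients who stop "will be contacted for safety evaluations during the 30 days following the last dose of study drug taken". Section 8.1 sets the same 30 days for SAE reporting. The Visit 7 description in Section 7 repeats the Week 24 assessments at the planned Month 6 date for early stoppers. Section 6.5.6 says that stopping treatment is not withdrawal from the study. Section 3 lists the incidence of CMV and BK virus infection at Month 6 as an objective.

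**The concern.** The trial asks whether a CNI-free regimen is as safe and well tolerated as standard treatment, and it is open-label, so its safety tables carry real weight.

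A relatedness item that names drugs of one arm only sets the other arm's count by definition, not by observation. A table of related events by arm would then look like a comparison without being one. The restriction acts when the investigator fills in the form, so programming cannot repair it afterwards.

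The 7-day rule works differently. It removes events from the tables only in patients who stop early, and some of them stop because of harm. In the Certican arm some will have had a long-acting antibody dose shortly before. An infection on day 10 after stopping may arise under that antibody's effect, is collected, and is then left out of the infection table.

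**Working it through.** The protocol gives no figure for either rule, so there is none to reproduce.

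**A. Relatedness: the texts side by side**
- Drugs to be rated (Section 7.6, item 2): Certican, Simulect dose 3, Simulect dose 4.
- Of these, given to control patients (Sections 4 and 6.1): none.
- Meaning of study drug in the opening paragraph of the same subsection and in the Glossary: includes the comparator.
- Table planned (Section 10.5.2): AE incidence by relationship to study drug.

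Under item 2 the number of suspected AEs in control is zero by definition. Under the wider definition it can be above zero. An investigator may follow either, so the control column has no fixed meaning.

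**B. Seven-day rule: collected against tabulated**

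Collection lasts 30 days after the last dose and tabulation stops at day 7, so 30 − 7 = 23 days per stopper are collected but not tabulated, before counting the Month 6 visit.

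**C. Is basiliximab still active at the cut?**

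Inputs from Section 1:
- One dose: 20 ± 7 days of receptor blockade. The protocol assumes that this period of "days in patients receiving only one injection of basiliximab is extended under concomitant administration of mycophenolic acid".
- Two induction doses (days 0 and 4): 36 ± 14 days.
- Triple therapy with cyclosporine, steroids and MMF: 59 ± 17 days.

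Let s be the days from the last extra dose to stopping. Treat the duration T as normal with the stated mean and SD (assumption). Then P(still saturated at the cut) = P(T > s + 7).

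Example, s = 14 and one dose: z = (21 − 20)/7 = 0.14, so P = 0.44.

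| s (days) | 20 ± 7 | 36 ± 14 | 59 ± 17 |
|---|---|---|---|
| 0 | 0.97 | 0.98 | >0.99 |
| 14 | 0.44 | 0.86 | 0.99 |
| 28 | 0.02 | 0.53 | 0.92 |
| 56 | <0.01 | 0.03 | 0.41 |
| 84 (Week 24) | <0.01 | <0.01 | 0.03 |

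**D. How many patients?**

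Assume stopping times uniform over Weeks 7 to 24 (17 × 7 = 119 days), dose 3 on day 0, and dose 4 on day 35 if still treated. The average probability is then 0.22, 0.46 or 0.72. A hand check with fixed mean durations agrees: the shares of stopping days with blockade left at the cut are (13 + 13)/119 = 22%, (29 + 29)/119 = 49% and (35 + 52)/119 = 73%.

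- 10% stopping (the planned drop-out rate in Section 10.7, used here as an assumption): 162 × 0.10 = 16.2 patients. Multiplied by 0.221, 0.464 and 0.718 this gives about 4, 8 and 12, or 2% to 7% of the arm.
- 30% stopping (assumption): 48.6 patients, giving about 11 to 35, or 7% to 22% of the arm.

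**E. What starts the clock?**

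The rule refers to stopping study medication. Section 6.5.1 uses study drug for everolimus, the Glossary for any required drug, and Section 10.3.1 treats study medication as each component of the regimen. On the everolimus reading the clock has no start in control. There is also a mismatch at the boundary: day 7 is excluded for AEs but included for laboratory values.

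**The case against.** **An on-treatment window is conventional.** The rule has the same wording for both arms and matches the windows for laboratory values and vital signs. Later events occur on replacement therapy and blur attribution. This stands as a reason to keep the 7-day table, but not as a reason to have no other.

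**A reader might infer that all safety tables are non-comparable between arms.** The documents do not support that. It is shown for the relatedness table only. The tables by body system, preferred term and severity are affected only through the number and timing of stoppers in each arm, which the protocol does not give.

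**A reader might infer that follow-up is cut.** It is not; tabulation is. All AEs stay in the listings with their dates. Discontinuation for adverse events is analysed under tolerability (Section 10.5.3) and within treatment failure (Section 10.5.1). The exclusion names the AE and infection tables, so loss from the separate tumor table is not established.

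**A reader might see a flat contradiction with the analysis period** "for the period between Week 7 (Baseline 2) and Month 6 (or date of premature discontinuation of the study" in Section 10.5.2. One sentence sets a period and the other sets treatment emergence within it, so they can coexist. The protocol is also divided on stoppers: Sections 6.5.2 and 6.5.5 speak of withdrawal from the study, while Section 6.5.6 does not regard them as withdrawn. Those places need reconciling.

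**A reader might state the loss as a share of patient-time.** If 24 of 162 patients (15%) stopped at Week 14, counting to Month 6 gives 24 × 9 = 216 of 162 × 17 = 2,754 patient-weeks (8%). Counting only the 30-day window gives 24 × 23/7 = 79 (2.9%). Both the stopping rate and the stopping time are invented for the example, and many of the 216 weeks fall after blockade would have ended.

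**The longer blockade figures come from another scheme.** The 36 and 59 days belong to induction dosing, the latter with cyclosporine and steroids. Doses 3 and 4 are five weeks apart and given without either. The single-dose figure is the closest match, and its extension under mycophenolic acid is itself an assumption of the protocol. The upper end of the range is therefore soft.

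**A control rate of exactly 0% related AEs is not certain**, because an investigator may apply the wider definition. The defect is the conflict itself.

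**Conclusion.** Both points hold within limits.

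On relatedness, item 2 of Section 7.6 conflicts with the definition of study drug in the same section and in the Glossary. Under either reading of investigator behaviour, the table by relationship does not support a comparison between arms. This needs no numerical assumption.

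On the 7-day rule, the summary tables leave out AEs and infections that the protocol collects and that bear on a stated Month 6 objective. The basiliximab argument applies to Certican patients who stop within weeks of the Week 7 or Week 12 dose. By Week 24 the last dose is 84 days old and blockade has ended in about 97% or more of patients. The size is modest and uncertain: about 4 to 12 Certican patients still saturated at the cut, given 10% stopping, uniform stopping times, normal durations and the range of blockade figures in Section 1. The single-dose figure gives the lower end. The actual effect on the tables cannot be known from the protocol.

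**What to change.** 1. Reconcile Section 7.6 item 2 with the definition of study drug in that section and in the Glossary. Either record relationship to any component of the assigned regimen (Sandimmun Optoral, Myfortic, Certican, Simulect) in both arms, or present related AEs for the Certican arm only and make no comparison.
2. Add to Section 10.5.2 a table of all AEs, infections and tumors from Baseline 2 to Month 6, by randomized arm, in all randomized and treated patients. Keep the 7-day on-treatment table beside it.
3. State which drug's discontinuation starts the 7-day clock in each arm, and treat day 7 alike for AEs and laboratory values.
4. Reconcile the statements on whether patients who stop treatment remain in the study, since the all-events table relies on their follow-up to Month 6.

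The cost is one CRF field definition, some wording and one extra set of tables from data already planned for collection. The downside is that some events on replacement therapy enter the all-events table, which is why the on-treatment table should stay.

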## **Laboratory data**

Abnormalities according notable criteria (see [Appendix 2](#)) will be identified. The proportions of patients with clinically notable abnormalities according to the notable criteria will be summarized. Shifts from baseline value to worst post-baseline value based on the normal ranges will be presented graphically ([Amit et al., 2008](#)). The worst observation is defined as the highest or lowest measure during the different observations periods whereby high or low are chosen according to the direction of abnormality. Further, descriptive statistics of change from baseline of all laboratory variables will be presented by visit. A by-patient listing of all clinically notable abnormal laboratory data will be generated. Only assessments obtained up to 7 days after the discontinuation of study medication will be considered “on-treatment” and analyzed with relationship to immunosuppressive therapy.

The relative frequency of proteinurea will be tabulated by treatment group and visit.

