## 3 Objectives

The primary objective of this trial is to demonstrate superiority of a treatment regimen with Certican with respect to the renal function at 6 months after renal transplantation (Tx) assessed by glomerular filtration rate (GFR) – Cockcroft-Gault method - as compared to the standard regimen in *de novo* senior renal transplant recipients.

Secondary objectives of this trial are:

- to assess renal function by GFR – MDRD and Nankivell method – at Month 6 post Tx
- to assess renal function by serum creatinine at Month 6 post Tx
- to assess efficacy (biopsy proven acute rejection, graft loss, death) at Month 6
- to assess occurrence of treatment failures up to or at Month 6, while treatment failure is defined as a composite endpoint of biopsy proven acute rejection, graft loss, death, loss to follow up and discontinuations due to lack of efficacy or toxicity, or conversion to another regimen (at least one condition must be present)
- to assess evolution of renal function (creatinine slope) between Week 7 (randomization) and Month 6
- to assess CD25 saturation on lymphocytes
- to assess safety and tolerability at Month 6:
  - AE/SAE
  - incidence of infections (CMV, BK virus)
  - tumor incidence
  - cardiovascular risk
  - occurrence of proteinuria
  - NODM

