#### **Inclusion Criteria**

1. Patients with an stable serum creatinine < 3.0 mg/dl
2. Patients have to be on an immunosuppressive regimen with  $\geq 720$  mg/d Myfortic® and Sandimmun® Optoral
3. Patients with a proteinuria < 500 mg/g creatinine

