### **Laboratory evaluations**

The center's local laboratory will be used to analyze the clinical laboratory data during the study.

The following variables will be examined:

Hematology: Hemoglobin, leukocytes (differential blood count), absolute neutrophil count and platelet count, hematokrit (HK)

Blood chemistry: creatinine, urea, sodium, potassium, calcium, ALAT, ASAT, protein, AP, albumin, C-reactive protein (CRP), phosphate, magnesium, CPK

Additionally at Baseline Visit 1 (= extended program):  
total cholesterol, LDL, HDL, triglycerides,

Additionally at Baseline Visit 2 and Month 6  
(= complete program):

glucose (fasting), ferritin, transferrin, serum iron  
total cholesterol, LDL, HDL, triglycerides,

Viral Serology: Hepatitis B (HBsAg), Hepatitis C, HIV (only at Baseline visit 1), CMV

Urinalysis: creatinine, protein, albumin

For determination of the drug levels see [Section 7.9](#).

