## **10 Statistical methods**

The data will be analyzed by Novartis and/or by the designated CRO. Any data analysis carried out independently by the investigator(s) should be submitted to Novartis before publication or presentation. The final analysis will be done when all patients have completed the study treatment at Visit 6 (Week 24/Month 6) or discontinued prematurely. It is planned that the data from all centers that participate in this protocol will be used, so that an adequate number of patients will be available for analysis.

Data will be summarized with respect to demographic and baseline characteristics, efficacy observations and measurements, safety observations and measurements, and pharmacokinetic measurements. All summary statistics will be presented by

treatment group. Categorical variables will be summarized by absolute and relative frequencies. Continuous variables will be summarized by descriptive statistics of mean, standard deviation, minimum, median and maximum. Time-to-event data including rates of affected patients will be assessed by Kaplan-Meier statistics.

The assessment of safety will be based mainly on the frequency of adverse events and on the number of laboratory values that fall outside of pre-determined ranges. Other safety data (e.g. electrocardiogram, vital signs, special tests) will be considered as appropriate. Adverse events will be summarized by presenting, for each treatment group, the number and percentage of patients having any adverse event, having an adverse event in each body system and having each individual adverse event. Any other information collected (e.g. severity or relatedness to study medication) will be listed as appropriate.

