### **10.7 Sample size calculation**

From data for the subgroup of elderly patients in study CRAD001A2418, the probable difference in the GFR (Cockcroft-Gault) between the CNI-free regimen group and the standard regimen group is estimated as  $\delta = 8$  ml/min with a standard deviation of 16 ml/min at Month 6 after transplantation. Assuming a difference in the mean GFR of 8 ml/min (60 ml/min in the CNI-free group and 52 ml/min in the standard regimen group) and a common standard deviation of 19 ml/min, a two-group t-test with a 5% two-sided significance level will have 80% power to detect this difference when the sample sizes in the CNI-free group is 135 and in the standard regimen group is 68, respectively (a total sample size of 203). Taking into account a common drop-out rate of 10%, 162 patients need to be randomized into the CNI-free group, and 82 into the standard regimen group (a total drop-out adjusted sample size of 244 patients). Enrollment will be continued until the required sample size will be achieved.

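### The only proteinuria-specific analysis is a yes/no frequency by arm and visit; a BL2-adjusted model of the urine protein/creatinine ratio would compare the arms more precisely at little cost

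*Protocol*

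**What the plan says.** Section 3 lists "occurrence of proteinuria" among the secondary safety objectives, and section 10.5.2 lists "Occurrence of proteinuria" among the safety variables. Under Laboratory data in 10.5.2, the only sentence specific to it is: "The relative frequency of proteinurea will be tabulated by treatment group and visit". No cut is given there, and Appendix 2 has no urine criterion.

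The data are richer than a yes/no. Section 7.6 lists "Urinalysis: creatinine, protein, albumin", and Table 7-1 schedules urinalysis at Weeks 2, 7, 12, 18 and 24. The ratio is already in use: BL2 entry in section 5 requires "Patients with a proteinuria < 500 mg/g creatinine".

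The same Laboratory data paragraph also has a general provision: "Further, descriptive statistics of change from baseline of all laboratory variables will be presented by visit". Section 10 adds "All summary statistics will be presented by" treatment group.

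**The concern.** Cutting a continuous measurement into yes/no loses information. Eligible patients enter the randomized phase below 500 mg/g, the only proteinuria limit in the document. If a cut near that value were used, a rise from, say, 150 to 400 mg/g would not be counted.

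The study asks whether the CNI-free regimen is as safe as standard treatment while benefiting renal function. A change in urinary protein is part of reading a GFR gain, and the planned table is a blunt way to see one. Other exploratory variables get more: MDRD and Nankivell GFR and serum creatinine each have an ANCOVA modelled on the primary analysis (10.5.1), and tolerability gets Fisher's exact test (10.5.3).

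**Working it through.** **Inputs from the protocol (10.7).** Difference 8 ml/min, SD 19 ml/min, allocation 2:1, two-sided 5%, 80% power, evaluable n = 135 and 68. These are GFR figures; none is given for proteinuria.

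**The plan's own figure.** The protocol states that "a two-group t-test with a 5% two-sided significance level will have 80% power" at 135 + 68 = 203.
- Control n = (1 + 1/2) × (1.96 + 0.842)² × 19²/8² = 66.4, so 67, with 134 in the other arm: 201 in all.
- Noncentral-t power at 68/135 is 0.805.

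The 203 is reproduced, and I use 68/135 below as the assumed number with a Month 6 urine value.

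**Step 1: efficiency of a yes/no frequency.** Assume the log ratio is normal with equal SD in both arms. For small shifts, and with φ taken at the cut that gives control prevalence p, the efficiency relative to the continuous value is

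RE = φ(z)² / [p(1 − p)], with z = Φ⁻¹(1 − p).

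Example for p = 0.20: z = 0.842, φ = 0.280, RE = 0.0784/0.16 = 0.49.

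For power, assume a shift of d = 0.42 SD (the primary effect, 8/19, borrowed for illustration). The prevalence in the Certican arm is then 1 − Φ(z − d).

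| Assumed control prevalence | Certican prevalence | RE | Power, frequency | Power, continuous |
|---|---|---|---|---|
| 5% | 11.0% | 0.22 | 0.27 | 0.80 |
| 10% | 19.4% | 0.34 | 0.40 | 0.80 |
| 20% | 33.7% | 0.49 | 0.53 | 0.80 |
| 30% | 45.8% | 0.58 | 0.59 | 0.80 |
| 50% | 66.3% | 0.64 | 0.61 | 0.80 |

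No proteinuria test is planned, so interval width is the more direct reading. An interval for the same underlying shift is wider by 1/√RE: 1/√0.224 = 2.1 times at 5% prevalence and 1/√0.637 = 1.25 times at 50%.

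**Step 2: the same on the mg/g scale.** Assumptions: log-SD 0.9, a 1.5-fold rise, control median 120 or 200 mg/g, correlation 0.5 between BL2 and Month 6.
- Standard error factor: √(1/68 + 1/135) = 0.149.
- Log ratio, unadjusted: ln(1.5)/0.9 = 0.451; 0.451/0.149 = 3.03; power 0.85.
- Adjusted for BL2: SD = 0.9 × √(1 − 0.5²) = 0.779; ln(1.5)/0.779 = 0.520; 0.520/0.149 = 3.50; power 0.94.
- Cut at 500 mg/g: 5.6% against 12.8% above the cut with median 120 (power 0.33), and 15.4% against 28.5% with median 200 (power 0.54).
- Cut at 300 mg/g: 15.4% against 28.5% with median 120 (power 0.54), and 32.6% against 50% with median 200 (power 0.66).

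The continuous analysis is ahead in each case. The size of the gap depends on the assumed median and cut. With larger effects it shrinks, because both analyses approach 100% power.

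**The case against.** The strongest reply has four parts.

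- **The continuous values are not ignored.** A reader might infer that proteinuria is reduced to a dichotomy and nothing else. The documents do not support that. On its wording, the general line on change from baseline covers urine protein, albumin and creatinine by visit, and shift plots to the worst value are planned as well. This stands. What it leaves out is the ratio, which the protocol itself uses at entry, and any BL2-adjusted contrast with an interval.
- **The table fits the objective as worded.** The objective speaks of occurrence, and a frequency answers it. This also stands, and is why the table should remain.
- **No test is planned, so power has no direct object.** Correct; the power figures only illustrate lost precision. Statistical analysis plan (SAP) content, which is not shown, could also supply a cut or a ratio analysis, so the missing cut is not counted as a fault here.
- **The loss may be moderate.** A reader might infer that most of the information is discarded. That holds only at control prevalences of about 20% or less. At 30% to 50% the loss is 42% to 36%.

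A reader might also take the background (section 1) as naming on-treatment proteinuria the main prognostic factor for CNI withdrawal. It does not. The statement concerns baseline proteinuria above 800 mg/day in chronic transplant patients, a selection factor for which the trial has its own BL2 entry limit.

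**Conclusion.** The point holds as a modest improvement. The only proteinuria-specific analysis is a yes/no frequency, although the data for a more precise one are already collected and the ratio is already used at BL2. Compared with the continuous value, the frequency keeps roughly 22% to 64% of the information over assumed control prevalences of 5% to 50%, before any gain from BL2 adjustment. These figures rest on a log-normal ratio, equal SDs in the two arms and prevalences that the protocol does not give. The direction does not depend on the cut; the size does. Neither the primary analysis nor the sample size is affected.

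**What to change.** Keep the frequency table. Add to 10.5.2, as an exploratory analysis in the full analysis set by assigned arm:

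> The log-transformed urine protein/creatinine ratio (mg/g) at Month 6 will be analyzed by ANCOVA with treatment, center and pre-randomization rejection as factors and the log ratio at BL2 as covariate; the ratio of geometric means with 95% CI will be reported, with geometric means by visit.

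The analysis set must be named, because the safety set used elsewhere in 10.5.2 includes transplanted patients who were never randomized (10.1). Handling of missing values can go in the SAP.

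Cost: one more exploratory model on data already collected, with no new visits and no claim on the 5% significance level. A ratio of geometric means is less familiar to clinicians than a percentage, which is a further reason to keep the table.
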